### Interim analyses {21b}

No interim analysis will be performed on the epidemiological data collected from the intervention period post-randomization.

### Methods for additional analyses (e.g. subgroup analyses) {20b}

The per-protocol (PP) population includes the participants from the ITT population who are treated following the specifications of the study protocol without major protocol deviations.

#### Participants who move to a new house during the intervention follow-up period

For a participant who moves to a different house within the same cluster, that participant will be included in both the ITT and PP analyses. The HH characteristics will be updated at the time the subjects moved.For a participant who moves to a different house in a different cluster, the data from the participant before the participant moves will be included in the ITT analysis. All data from the participant will be included in the PP analysis, both the treatment information and the HH characteristics will be updated at the time the participants moved.

#### Participants who are hospitalized for serious complicated illness (e.g., chronic illness), die, drop out, or miss scheduled visits due to reasons not related to the malaria outcome or intervention during the follow-up period

For participants that fall under this category, the available data from the participants (up to the time point when the participants are hospitalized, die, or drop out; data from the scheduled visits that the participants did not miss) will be included in both the ITT and PP analyses as the missing or absent data can be ignored.

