## Assignment of interventions: blinding

### Who will be blinded {17a}

The Sponsor, study PI, and staff will not be blinded to cluster assignment (SR delivery channel). There will be no placebo integrated into the study design, as the SR intervention will have already been evaluated for efficacy under controlled conditions.

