#### Follow-up of the cohort

All efforts to overlay the commencement of enrollment with the start of the malaria transmission season will occur; however, programmatic timelines may not allow for perfect alignment. The 12-month follow-up period will ensure estimating potential changes in malaria incidence during anticipated seasonal malaria transmission peaks.

The distribution of the SR will occur after enrollment. At this time, cohort participants will be presumptively cleared of parasites with a treatment dose of AL unless they have recently been treated (within the last 2 weeks). This will be done so that the incidence of malaria infection following study product deployment can be measured.

Participants enrolled in the cohort will be followed every 2 weeks for malaria infection during the 12-month period after the study product has been distributed. All cohort participants and HH residents will also be informed to come to the nearest health facility for unscheduled sick visits, as needed. If the participant presents with a history of fever in the last 48 h, a RDT will be performed and AL will be administered if the RDT is positive for malaria.

Every 2 weeks, study team data collectors will visit the enrolled HHs. At each data collection HH visit, the parent/guardian will be asked about the recent use of ITNs and other vector control interventions as well as recent history of illness, recent travels outside the HH, and recent use of anti-malarial drugs.

During the first scheduled HH visit, a blood sample will be taken for malaria RDT (Monthly Visit #1). During the second scheduled HH visit, a blood sample will only be taken if the participant has a recent history of fever (Monthly Visit #2). The total blood volume for samples at each visit will not exceed 500 mli. A second blood sample may be taken for hemoglobin testing during follow-up only if the data collection/clinical team suspects anemia in participating children.

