### Adverse event reporting and harms {22}

An AE includes any noxious, pathological, or unintended change in anatomical, physiological, or metabolic functions as indicated by physical signs, symptoms, and/or laboratory-detected changes occurring in any phase of the clinical study associated with the study intervention. This definition includes an exacerbation of pre-existing conditions or events, intercurrent illnesses. A SAE is any untoward medical occurrence that results in death, is life-threatening, results in persistent or significant disability/incapacity, requires in-patient hospitalization or prolongation of existing hospitalization, or is a congenital anomaly/birth defect in the offspring of a study participant. In addition, important medical events that may jeopardize the participant or may require intervention to prevent one of the other outcomes listed above will be considered serious.

All SAEs will be recorded on the appropriate SAE case report form, followed through resolution by a study physician, and reviewed by a study physician.

Symptomatic uncomplicated or severe malaria infection will be coded as AEs as will any other acute illness, throughout the 12 months of the study follow-up phase. Clinical malaria will be recorded in the same fashion as other AEs. In general, uncomplicated malaria will constitute an AE and severe malaria will constitute an SAE. Anticipated day-to-day fluctuations of pre-existing conditions that do not represent a clinically significant exacerbation need not be considered AEs. Discrete episodes of chronic conditions occurring during a study period will be reported as AEs to assess changes in frequency or severity. Pre-existing conditions or signs and/or symptoms (including any that are not recognized at study entry but are recognized during the study period) present in a participant prior to the start of the study will be recorded on the participant’s Case Report Form.

AEs will be documented in terms of a medical diagnosis. When it is not possible to make a specific medical diagnosis, the AE will be documented in terms of signs and/or symptoms observed by the investigator or reported by the participant at each study visit. Any hospitalization will be considered a SAE.

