AEs to be recorded as endpoints will be pre-defined based on SCJ toxicology reports of “probable,” “possible,” “plausible,” and “unlikely”:Probable: sensory irritation (oral and dermal)Possible: nausea/vomiting (oral), skin irritation/rash (dermal), runny nose (inhalation)Plausible: salivationUnlikely: eye irritation, headache

AEs and SAEs will be recorded throughout the study. SAEs and the study reports will also be provided to the Makerere University School of Public Health Research and Ethics Committee as required by their current Standard Operating Procedures. AEs will be recorded at time of product replacement and/or when a participant reports for malaria testing. In addition, participants will be informed they can contact study staff anytime they experience an AE. SAEs will be recorded at time of death, hospitalization. Assessment of SAE relatedness to intervention will be conducted by the health facility physician and the study coordinator, in coordination with the local PI in-country with confirmation/verification by the DSMB Medical Monitor based on the study clinician SAE report and trends in other SAE datasets.

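### Children hospitalised for a serious unrelated illness have their data cut at admission in both ITT and PP, although admission does not by itself end follow-up

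*Protocol article*

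**What the plan says.** The rule stands in the protocol article under Methods for additional analyses {20b}. Its heading names four groups: children in hospital with serious complicated illness (chronic illness is the example given), children who die, children who drop out, and children who miss visits. In each case the reason must have nothing to do with malaria or the product. A parenthesis then says which data are used. The first clause covers data "up to the time point when the participants are hospitalized, die, or drop out"; the second covers "data from the scheduled visits that the participants did not miss". These data "will be included in both the ITT and PP analyses as the missing or absent data can be ignored".

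Other sections bear on it:

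- Follow-up of the cohort: "Participants enrolled in the cohort will be followed every 2 weeks for malaria infection during the 12-month period" once the product is in place.
- Criteria for discontinuing {11b}: staff may end a child's participation if inclusion criteria are no longer met or after clinical assessment of an adverse event. This is discretionary.
- Missing data {20c}: after ignorable missed visits or drop-out, everything available from the child is analysed. Hospitalisation is not mentioned.
- Adverse event reporting {22}: "Any hospitalization will be considered a SAE". On causality, "Assessment of SAE relatedness to intervention will be conducted by the health facility physician and the study coordinator". The local PI is also involved, and the DSMB Medical Monitor verifies the result.
- Blinding {17a}: the sponsor, PI and staff know the allocation. Sequence generation {16a}: the DSMB is given the allocation code for safety assessments.

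**The concern.** The first clause puts hospitalisation on the same footing as death and drop-out. Those two leave nothing further to observe. A child who is discharged and stays in the study goes on having RDTs, so the results that the rule sets aside exist. An ignorability argument concerns data that were not observed and cannot justify leaving out data that were.

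The cut also depends on a label given after randomisation: the illness must be judged unrelated to malaria and to the intervention. The rule does not say who decides. If the decision follows the process for serious adverse events, it is made locally by people who can know the arm. The Medical Monitor verifies it, but belongs to a board that is given the allocation code. If admitted children have a different malaria risk and the label is applied differently across channels, the comparison called ITT is affected by that selection.

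The overall-infection analysis has most at stake, because repeat infections after discharge disappear. In the first-infection analysis, a child infected before admission has already left the risk set.

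**Working it through.** **1. Do the two clauses treat hospitalisation as truncation?** The heading lists hospitalised, die, drop out, miss visits. The first clause repeats the first three in the same order; the second answers the fourth. On the natural reading, hospitalised children belong to the truncated group, and no clause covers a child who returns.

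**2. Does this agree with neighbouring rules?** Missing data {20c} keeps all available data after missed visits or drop-out. Under {20b}, children with incomplete intervention stay in ITT as they are. Cutting at admission is stricter than either.

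**3. The plan's own precision figure, as a base.** Inputs from Sample size {14}: 16 clusters per arm, 40 households per cluster, coefficient of variation 0.40, 10% loss, incidence 0.5 to 1.0 per person-year. The 90% interval is from {20a}.

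- First infections per cluster: e = 40 × 0.9 × (1 − exp(−rate)) = 14.2 at rate 0.5 and 22.8 at rate 1.0.
- SE(log HR) = √[(2/16)(1/e + 0.40²)] = 0.170 and 0.160.
- 90% interval at HR 1, exp(±1.645 SE): 0.756 to 1.322 and 0.769 to 1.300.

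The plan gives upper bounds of 1.30 to 1.33 and lower bounds of 0.77 to 0.75, so its figure is reproduced within 1%.

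**4. Person-time lost.** Let h be the share of children with such an admission in 12 months. It is **assumed**, because the protocol gives no rate. With constant hazard r = −ln(1 − h), the share of person-time lost by stopping at first admission is 1 − h/r. If visits after discharge are kept and about two weeks are missed per admission (also assumed), it is r × 2/52. Planned person-years per arm: 16 × 45 × 0.9 = 648.

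| h | lost if cut at admission | person-years per arm | lost if visits after discharge are kept |
|---|---|---|---|
| 1% | 0.5% | 3.2 | 0.04% |
| 2% | 1.0% | 6.5 | 0.08% |
| 5% | 2.5% | 16.3 | 0.2% |
| 10% | 5.1% | 33.0 | 0.4% |

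**5. Precision.** At 45 households and rate 0.5, e = 45 × 0.9 × 0.3935 = 15.9 and the upper bound is 1.316. With 5.1% fewer, e = 15.1 and the bound is 1.319. The change is negligible, and even this overstates the loss for first infections.

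**6. First-infection analysis.** At a constant rate of 0.5 to 1.0, a child admitted at mid-year is still uninfected with probability exp(−0.25) = 0.78 to exp(−0.5) = 0.61. The other 22% to 39% are not affected in that analysis.

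**7. Possible bias (overall infections, crude rate ratio, no true difference between arms).** Assume a share s of children is admitted at mid-year with f times the usual malaria rate, and a fraction q of them is labelled unrelated and cut. The arm's relative rate is

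[(1 − s) + s·f·(1 − q/2)] / [(1 − s) + s·(1 − q/2)].

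- Same s, f and q in both arms: the ratio is 1.
- q = 1 in one arm and 0.5 in the other: with s = 5%, f = 1.5, 1.0190/1.0128 = 1.006; with s = 10%, f = 3, 1.1538/1.1053 = 1.044.
- q = 1 against 0: 1.025/1.0128 = 1.012 and 1.200/1.1053 = 1.086.

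The shift is thus 0.6% to 4.4% with labelling half as frequent in one arm, and 1.2% to 8.6% if it is wholly one-sided.

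**The case against.** The strongest reply is that this is loose drafting. The main clause speaks of available data, and a visit after discharge is both available and not missed; {20c} also favours using everything. That reading is possible. But it needs the second clause to override the first, which names hospitalisation expressly, and two analysts could build different datasets from the same text.

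A second reply is that follow-up may really stop for some of these children. Eligibility {10} refers to absence of other serious illness and to nights slept in the cluster, and {11b} lets staff end participation. This stands for those children. Termination is discretionary, however, so it does not cover those who stay in.

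Third, {20c} requires reasons for missingness and the missing fraction to be reported by arm and cluster. This could reveal an imbalance but would not restore the data.

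A reader might also infer more than the text supports:

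- *Every admission triggers the cut.* All admissions count as serious adverse events, but this rule covers only serious complicated illness unrelated to malaria or the product. The national share of admissions not due to malaria therefore cannot size it.
- *Later serious adverse events are lost.* The rule governs the ITT and PP analyses. Adverse events are recorded throughout and summarised among enrolled participants.
- *Children admitted for malaria keep their later data.* The rule is silent on them.
- *Unblinded staff alone decide.* The rule names no one; {22} concerns relatedness to the intervention and includes the Medical Monitor's verification.
- *The loss adds to the planned 10%.* Sample size {14} does not say what that 10% includes.

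**Conclusion.** The point holds in limited form. As written, the rule ends the analysed data of a defined group at admission, in both ITT and PP, without accounting for children who are discharged and remain under observation. It fits poorly with {20c}, and it makes inclusion depend on a post-randomisation judgement with no named judge in an open-label trial.

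The likely numerical effect is small: about 0.5% to 5% of person-time if 1% to 10% of children are affected, and almost no change in interval width. The hazard ratio is at material risk only if labelling differs by arm, and the shifts shown for that case rest wholly on assumed admission shares, relative malaria rates and labelling patterns. They should also be read against a planned 90% interval of roughly 0.75 to 1.33 in a trial described as exploratory and without formal hypothesis testing. The reason to correct the rule is the validity of the ITT analysis, not precision.

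**What to change.** Amend the {20b} rule so that data end only at death, withdrawal (including participation ended by staff) or loss to follow-up. Treat visits missed during an admission as missed visits. Include all visits and infections after discharge in ITT, and in PP where the child otherwise qualifies, whatever the cause of admission. The relatedness judgement then no longer decides which data an admitted child contributes. The separate rule on moves between clusters is untouched.

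The cost is one sentence in the analysis text, made before the data are analysed. The two-weekly visits are already planned, so no new data, visits or participants are needed.

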#### Participants who do not receive (complete) intervention due to traveling outside, mis-application, or partial application of the product

For the ITT analyses, these participants will be included as is. For the PP analysis, “travel outside” (Y or N; an individual-level covariate) and the product application rate in each HH (expected to be close to 100%) will be included as covariates if the data are not overly imbalanced between the Y and N categories for “travel outside”, and there is practically/clinically.

The primary analyses will also be carried out in the PP population, with some modification on the covariate list in the cloglog models for the first-time infection and the overall infection. Specifically, for the PP analysis, “travel outside” (Y or N; an individual-level covariate), and the product application rate in each HH (expected to be close to 100%), the coverage rate of the product in each cluster, will be included as covariates if the data are balanced between the Y and N categories for “travel outside” and there is practically/clinically meaningful variation in the product application rate across HHs and clusters and in the coverage rate across clusters.

For both the ITT and PP analysis and in the cloglog models for the first-time infection and the overall infection, in addition to the HH-level covariates listed above (number of doors, open eaves or not, and wall type), we will also perform a supplementary analysis by including bednet usage in the last 24 h as an additional covariate, which is a post-randomization covariate.

The first and overall malaria incidence rate per person-year during the follow-up will be calculated for each treatment arm. Since the malaria incidences are interval-censored, the mid-point between two visits will be imputed as the time at risk for a malaria event. The average incidence rate within each arm will be calculated, together with the coefficients of variation.

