#### VHT distribution channel

Uganda’s national community health worker program is organized as VHTs who serve as a HH’s first point of contact for various health-related issues. Working primarily as volunteers, VHTs are ordinary community members who receive basic health care training to provide home visits and health management services. CRS will recruit approximately 32 VHTs to distribute SR, collect and dispose of old SR, and provide HH-level education about SRs. VHTs will be recruited from the existing VHT pool, which was identified and trained by the MOH. Lists of active VHTs are available at the health facilities and with the health cluster lead agency. All the VHTs in the refugee settlement have experience implementing integrated Community Case Management (iCCM) for childhood illness and the provision of other interventions such as ITN, immunization, and health education. Once recruited, the VHTs will receive additional training with regards to study procedures around the SR product itself, how to hang, remove, and safely dispose of it, as well as documenting and monitoring the process. VHTs recruited for study activities will also receive a remuneration for their activities based on locally approved rates.

Upon enrollment into the study, HH participating in clusters assigned to the VHT distribution channel will be visited monthly by a trained VHT. During the home visit, the VHT will distribute the appropriate number of SRs based on measurements for all structures in the HH. They will also retrieve used SR and dispose appropriately. The VHTs will track distribution and retrieval and follow-up on discrepancies as needed to ensure safe product disposal according to the manufacturer’s instructions. During the home visits, VHTs will share key educational information about malaria prevention, the SR, including appropriate placement on the walls, safety, side effects, etc. The study team will check to see if the SRs are hung appropriately and address any issues with the residents. VHTs will address any questions or concerns the participating HH might have.

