#### Enrollment of the cohort

A cohort of children aged ≥ 6 months to ≤ 59 months will be enrolled within each cluster to assess the effectiveness of the SR product against the contemporaneous control and in additional clusters to estimate effectiveness using programmatic delivery systems. HHs will be randomly selected from the master list of HHs obtained during ramp-up phase mapping to achieve the desired sample size.

Selected HHs based on cluster maps will be visited and if a child is present, the study will be explained and consent obtained from the child’s primary caregiver before screening for eligibility and enrolling him/her in the study. All eligible children in a selected HH will be invited to participate. (See above for a more complete description of the consent process.) At enrollment, the study team will have a list of all age-eligible children in each HH selected. These data will have come from the initial mapping and census of the study clusters. At the time of participant recruitment, the tablet will randomly select one of the age-eligible children for the field staff to screen for inclusion and exclusion criteria, which includes a hemoglobin test. Prior to screening, the team will obtain parental/caregiver consent. If there are no eligible children in the HH after screening, a new HH will be randomly selected from the HH listing exercise (mapping and census).

At enrollment, the age and gender of the child will be recorded and the parent/guardian (as needed) will be asked about the use of ITNs and anti-malarial drugs. Contact information, as available, will be captured. A fingerstick blood sample will be taken for a malaria RDT, and a hemoglobin level will be evaluated in a capillary sample using the HemoCue device**.** The study team will work with local health partners and the district health department providing iCCM to make sure children in need of iron supplements and antihelminths are managed according to national protocols and coordinate any referrals or follow-ups as needed. If the screened child does not meet the inclusion criteria, the tablet will randomly select another child from the remaining age-eligible children in the same house. The process will continue until one of the children is successfully enrolled.

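### A single travel yes/no per child in the per-protocol hazard models can depend on length of follow-up, and same-visit net use in the supplementary analysis describes a night after infection

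*Protocol article*

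**What the plan says.** All references are to the protocol article; the SAP is not shown.

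- **Travel.** The subsection of Methods for additional analyses {20b} on participants who do not receive the complete intervention defines travel as "Y or N; an individual-level covariate". In the per-protocol models, travel and the product application and coverage rates "will be included as covariates if the data are balanced between the Y and N categories for" travel. In the intention-to-treat analysis travel is not adjusted for: "For the ITT analyses, these participants will be included as is".
- **Net use.** The same subsection states "we will also perform a supplementary analysis by including bednet usage" in the last 24 hours. This applies to the intention-to-treat and per-protocol analyses, for first and overall infections. It is entered "as an additional covariate, which is a post-randomization covariate".
- **Model.** Statistical methods {20a} gives the hazard a time index but gives the covariate vector none. Time-updating is stated only for children who move house.
- **Data collection.** Under Follow-up of the cohort, at every two-weekly visit "the parent/guardian will be asked about the recent use of ITNs and other vector control interventions", and about recent travel. The RDT is done at Monthly Visit #1, and at Visit #2 only after recent fever.
- **A possible route to net use.** Under VHT distribution channel, at home visits "VHTs will share key educational information about malaria prevention".

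**The concern.** Travel varies over time, but the model gives each child one value. In a first-infection model a child's observation ends at infection. If the yes/no means any travel reported up to that point, an early infection leaves few visits at which travel can be reported, and a child who stays uninfected has the whole year. The coding then depends on the outcome, and travel looks protective even when it is not. If travel also differs by arm, the error carries over to the channel comparison.

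For net use the issue is timing and meaning. Infection is acquired at some time between tests, so last night's net use reported at the detecting visit cannot have influenced it, and a sick child may have been put under a net since. If a channel changes net use, adjusting for it also removes part of that channel's effect. A reader who takes these results as checks on the primary hazard ratio could be misled.

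**Working it through.** The documents give no travel, net-use or net-efficacy figures, so all such inputs below are assumptions.

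**1. Yardstick: the plan's own interval.** Inputs from Sample size {14}: 16 clusters per arm, 40 households per cluster, between-cluster CV 0.40, 10% loss, rate 0.5 to 1 per person-year. The 90% level is from {20a}.
- First infections per cluster: e = 40 × 0.9 × (1 − exp(−rate)), which is 14.16 at rate 0.5 and 22.76 at rate 1.0.
- SE(log HR) = sqrt((2/16) × (1/e + 0.40²)), which is 0.170 and 0.160.
- exp(±1.645 × SE) gives 0.756-1.322 and 0.769-1.300, within 0.01 of the stated bounds (0.75 to 0.77 and 1.30 to 1.33).

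**2. Chance of being coded yes.** With travel in a share q of four-week intervals, the chance of at least one report in k intervals is 1 − (1 − q)^k.

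| q | k = 3 | k = 13 |
|---|---|---|
| 5% | 1 − 0.95³ = 14% | 1 − 0.95¹³ = 49% |
| 10% | 1 − 0.90³ = 27% | 1 − 0.90¹³ = 75% |

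A child infected in the third interval is far less often coded yes than one never infected, with no effect of travel at all. The balance condition gives no protection, because shares near half are the ones that let the term in.

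**3. Effect on the travel coefficient.** Simulated first infections over 13 four-week intervals at 0.5 and 1.0 per person-year, cloglog fit with interval intercepts, no cluster effect:
- Travel in 5-10% of intervals, true travel HR 1.0 to 1.5: the any-travel-so-far coding gives about 0.35-0.49. A per-interval term recovers the true value.
- Travel in 3-8% of intervals, true travel HR 1: 0.38-0.48.

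**4. Effect on the channel HR.**
- Equal travel in both arms (3-8%), true channel HR 1.30: adjusted values 1.299, 1.289, 1.300 and 1.276, a shift of about 0.02 at most.
- Travel 5% of intervals in the reference arm and 10% in the other, true channel HR 1.00: 1.24-1.29. A crude hand check uses the k = 13 shares and a spurious travel HR of 0.40: (1 − 0.60 × 0.487) / (1 − 0.60 × 0.746) = 0.708 / 0.552 = 1.28. The per-interval term leaves the channel HR at about 1.00.

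**5. Net use.** Assume 70% use in the reference arm, 85% in the VHT arm, a net rate ratio of 0.6 and no direct channel effect.
- Total channel HR = (1 − 0.4 × 0.85) / (1 − 0.4 × 0.70) = 0.66 / 0.72 = 0.92. Correct adjustment gives 1.00, which is the effect not passing through nets and not the total effect.
- Simulated adjusted results when some non-using infected children are put under a net before the visit:

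| Net-use value entered | Net HR | Arm HR |
|---|---|---|
| Same visit, no switching | about 0.66 | about 0.99 |
| Same visit, 30% switch | 1.06-1.07 | about 0.92 |
| Same visit, 60% switch | 2.06-2.08 | 0.85-0.87 |
| Previous visit | 0.64-0.67 | 0.99-1.01 |

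With equal net use in the arms, the arm HR is unchanged by the adjustment.

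**The case against.** The strongest reply is that nothing here touches the main result. Travel enters only per-protocol models and only under a balance condition. Net use enters only a supplementary analysis, and the article itself labels it post-randomization. Neither is named for the primary model. All of this stands and sets the severity.

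A second reply is that the SAP may fix the coding, and that calling travel individual-level states its level without saying that it is constant in time. This stands in part. The bias in steps 2 to 4 is conditional on accumulating reports up to first infection. It does not arise in the same way in the overall-infection model, where infection does not end follow-up. But a yes/no per individual, beside covariates with no time index, is what the article writes.

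Three stronger readings are tempting and are not supported:
- *Both covariates are recorded after the infection.* Both are asked every two weeks, so earlier values exist, and travel is a look-back item that can cover the exposure period. Its fault is the single coding. For net use, the detecting-visit value is the natural reading but is not stated.
- *The VHT channel changes net use.* The article says only that VHTs give prevention education. Every enrolled child receives an ITN and all participants are encouraged to use one, so an arm difference is possible and not shown.
- *The travel term pulls the channel HR toward 1.* With equal travel the shift is negligible, and with unequal travel its direction depends on which arm travels more.

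**Conclusion.** The point holds as a minor one. A travel yes/no accumulated to first infection gives a travel coefficient well below 1 (about 0.35-0.49) whether or not travel matters. The per-protocol channel HR is distorted materially only if travel differs by arm: a shift from 1.00 to about 1.25 is comparable with the distance from 1 to the plan's own upper bound of 1.30-1.33, but it rests on an assumed twofold difference in travel. With equal travel the channel HR is essentially unchanged.

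Same-visit net use can misstate the net coefficient if behaviour changes with illness. It misstates the channel HR only if net use also differs by arm. Even a correctly timed net-adjusted HR is not the total channel effect. The primary intention-to-treat HR is unaffected throughout.

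**What to change.** 1. In the per-protocol models, replace the single travel value by a time-varying yes/no for the interval leading up to each test, built from the two-weekly reports.
2. In the supplementary net-use analysis, enter net use as a time-varying term taken from the visit before the detecting interval, and name that visit.
3. Add one sentence saying that the net-adjusted HR is not the total effect of the delivery channel.

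The cost is analysis wording and some data preparation; the items are already collected at every visit. Replacing follow-up net use by net use at enrolment is not required: the enrolment answer comes before every child receives a new ITN and would answer a different question.
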